#### 2.2.4. Patient Inclusion

When the PHC practitioner identifies a potential participant, they will fill out a referral form indicating that the patient meets the criteria and then provide the patient with an information leaflet. The health care professional will inform the researcher once the patient has confirmed their consent. The evaluating researcher will then contact the participant and confirm whether or not they will be included in the study based on the inclusion and exclusion criteria. 

#### 2.2.5. Randomisation, Allocation and Masking of Study Groups

Once baseline data have been collected, the participants will be randomised. An independent statistician will perform the individual randomisation using a computer-generated random number sequence (blinded sequence). The randomisation will be carried out using a list of patients (Figure 2). Given the nature of the interventions, participants will not be blind to their allocation. A researcher will call them to explain their assigned intervention and will request that participants do not inform other researchers of their allocation.

#### 2.2.6. Intervention

1st Recommended treatment (TAU) prescribed by health care professionals in accordance with NICE Guidelines and CAMFiC’s Manifestaciones persistentes de la COVID-19: Guía de práctica clínica [Ongoing manifestations of COVID-19: Clinical Practice Guidelines] and its subsequent updates.

2nd TAU plus the use of the APP as a community resource + three face-to-face motivational interviewing sessions to increase adherence. 

The content of the APP is based on scientific evidence that aims to alleviate the symptoms of patients diagnosed with long COVID-19 [48,49,50,51,52]. Depending on their health status, the participants will find all the advises useful, or only those that respond to their health needs based on the persistent symptoms they present will be helpful. However, it is emphasized that, if they cannot carry out any of the recommendations or exercises, or it causes them any type of discomfort, they should stop doing them immediately. The information provided in the APP has been divided into six work areas: (1) recommendations for following the Mediterranean diet; (2) recommendations for improving the sleep quality; (3) physical exercise recommendations with visual aids (i.e., charts); (4) respiratory physiotherapy exercises supported by video tutorials; (5) cognitive stimulation exercises with different levels of difficulty and (6) use of community resources. There is an additional section on behavioral activation and evidence-based documentation on managing long COVID-19. In all these sections, self-assessments and records are provided to record their activity so that patients can graphically observe their evolution over time as they continue to use the APP.

The content and operation of each of each section is detailed below:Diet

According to the Clinical Guide for Long COVID patient care of the Spanish Society of General and Family Physicians (SEMG) [49], eating habits should be taken into account to supply possible nutritional deficiencies. This APP aims to provide healthy eating pattern recommendations based mainly on the adherence to the classic Mediterranean diet. Specifically, the intake of vitamin D, vitamin B12, B complex, folic acid, and omega-3 fatty acids is recommended, according to some previous studies [53,54]. These nutrients are involved in the proper functioning of the metabolism, as well as in the immune system, so they could be beneficial for long COVID-19 patients. For the monitoring and evaluation of patients, this APP will offer a weekly evaluation based on 8 questions that will measure the patient’s adherence to the Mediterranean diet, showing an evolutionary chart of it.

2.Sleep hygiene

The quality of sleep and rest are fundamental components to feel physically and psychologically well. The amount of sleep needed varies by person and age, but most adults need between 7 and 8 h of sleep each night [55,56,57]. Given the great negative impact that has been found in various studies regarding the quality of sleep of long COVID-19 patients, it has been considered necessary to offer sleep guidelines to sleep well and improve rest [58,59]. However, in case of serious sleep problems, it is recommended to consult with a medical professional. This APP performs a daily evaluation of the self-perception that people have about their rest through 3 questions, presenting a history chart of it. 

3.Physical exercise

It has been shown that physical exercise can have benefits in multiple pathologies with which the long COVID-19 syndrome shares similarities both in its symptoms and possible pathogenic mechanisms. In this specific syndrome, the data are still insufficient, but the latest recommendations emphasize the need for personalized and symptom-adjusted physical activity to reduce long COVID-19 symptoms and promote recovery in these people [52]. Within this APP basic physical, exercises will be offered. This content was developed by a physiotherapist, and both the physical exercised and the instructions provided to the APP’s user patients were based on the recommendations proposed by different guides about the management of this disease or other pathologies with similar symptoms available in the current scientific evidence [50,51]. 

4.Respiratory physiotherapy

For the treatment of persistent respiratory symptoms, such as dyspnea, the different existing guidelines about the management of this disease recommend breathing exercises, that is, respiratory physiotherapy [49,51,60]. That is why a physiotherapist developed the respiratory exercises proposed in the content of this APP, based on the guidelines mentioned above. Similar to physical activity, this type of exercise must be graded and personalized to the characteristics of each patient, something that is stated in the instructions prior to carrying out these exercises.

5.Cognitive exercises

The most common cognitive impairment profile in long COVID-19 involves impaired executive function or planning, difficulty sustaining attention, decreased processing speed, deficits in short-term memory, abstraction and orientation, and even language impairment and anomie [61]. That is why an occupational therapist specialized in neurology developed three levels (i.e., easy, medium difficulty, difficult) of cognitive stimulation exercises aimed at working on all the cognitive skills that may be affected in the adult population with long COVID-19. In addition, a series of complementary voluntary activities were developed so that patients can stimulate all of the aforementioned within their activities of daily living (e.g., remembering a shopping list to stimulate memory).

6.Community resources: socialization and emotional well-being

This section, based on the effectiveness of RHA [20,21,22,23], mentioned in the introduction section, aims to improve the physical and emotional wellbeing of the participants through integration in the community, as well as socialization with peers. To achieve a good quality of life, it is not only essential to take care of our body through good habits, but also necessary to know how to live in the community (i.e., that our relationships with others are healthy). Therefore, the purpose of this section is to promote the participation in the process of local development through the use of different services, associations, or cultural activities, as well as groups affected by the same pathology.

In addition to the use of the APP, the intervention group will attend three face-to-face sessions held over three consecutive weeks with the aim of encouraging adherence to the APP, based on a motivational interview (MI). The first and second sessions will be individual, and the third will be a group session. All of them will be conducted by two study researchers with training to standardise the intervention, as well as with specific training, to carry out these sessions in accordance with Miller and Rollnick’s guidelines [62]. MIs will be conducted for 20–30 min, in alignment with the health belief model, which identifies the link between treatment adherence and health behavior [63,64,65].

This way of working follows Miller and Rollnick’s [62] definition of MI, which is “A collaborative, goal-oriented style of communication with particular attention to the language of change. It is designed to strengthen personal motivation for and commitment to a specific goal by eliciting and exploring the person’s own reasons for change within an atmosphere of acceptance and compassion”. Thus, MI is an interviewing method centred around the patient, which aims to evoke behavioural change by helping patients to understand and solve their problems [66]. Additionally, in the first session, the APP will be installed, and the participant will be taught how to manage and use it. The second session will be focused on sharing experiences of the first week of using the APP, addressing technological and content concerns, and setting goals they want to achieve through its use. The third session will be in groups (around 10–15 participants in each group) and will last for approximately one hour. In this last session, the benefits of using the APP and other community HAs as an adjuvant treatment will be discussed. 

#### 2.2.7. Variables and Instruments

An evaluation will be carried out at baseline with further assessments three and six months following the end of the intervention. The assessors administering the instruments will be blind to the type of treatment given to the patients. Patients will be contacted by phone at six weeks to monitor their adherence to APP recommendations and exercises in the intervention group and important changes in their health (e.g., reinfection) or treatment in both the control and intervention groups. 

The main variable will be quality of life, assessed by the SF-36 Questionnaire [67], which measures eight dimensions of health: physical function, physical role, aches and pains, general health, vitality, social function, emotional role, and mental health. In addition, it incorporates a declared health progress item. The eight dimensions define two main components of health: physical summary component and mental summary component, where scores above or below 50 indicate better or worse health status, respectively, than the mean of the reference population. The items are scored on Likert-type scales ranging from 1 to 3.5 or 6 depending on the type of item. The eight scales are scored from 0 to 100, with higher scores indicating better health status. The official Spanish version of the questionnaire [68] will be used.

Secondary results: The following variables will be collected

-Socio-demographic variables: gender, age, civil status, education, household, and occupation. Roles will also be collected using the Spanish version of the Role Checklist, whose test–retest reliability, measured by weighted Kappa, is 0.74 [69,70], an inventory divided into two parts. The first part evaluates the presence of the ten main roles of people’s life over time. Individuals should indicate whether they have performed each of the roles in the past (any time up to the week immediately preceding the assessment), whether they are currently being performed (on the day the checklist is completed and during the seven days prior), and if they plan to perform them in the future (any time from the following day). It is possible to mark more than one time for each role. The second part measures the value that the individual attributes to each role (“Not at all valuable”, “Somewhat valuable”, or “Very valuable”). People should mark the value they consider for each of ten roles, even if they have never played them or do not plan to do so in the future [71].-Clinical variables: clinical history, contraction of COVID-19, timeline of developing Long COVID, number of residual symptoms, and their severity measured via an analogue visual scale [72], days taken on sick-leave. Residual symptoms include: gastrointestinal symptoms, loss of smell, loss of taste, blurred vision, eye problems (increased dioptre, dry eyes, conjunctivitis), tiredness or fatigue, cough, fever (over 38 °C), low-grade fever (37–38 °C), chills or shivering without fever, bruising, myalgia, headaches, sore throat, dyspnoea, chronic fatigue, dizziness, tachycardia, orthostatic hypotension, joint pain, chest pain, back pain (cervical, dorsal or lumbar), neurological symptoms (tingling, spasms, etc.), memory loss, confusion or brain fog, short attention and concentration span, loss of libido or erectile dysfunction, altered menstrual cycle, urinary symptoms (infections, overactive bladder), hair loss, and other symptoms that can be considered residual [73,74].-Cognitive variables:(a)To assess the presence of cognitive impairment, the official Spanish version of the Montreal Cognitive Assessment (MoCA) [75,76,77] will be used, which is a test with adequate internal consistency (Cronbach’ alpha of 0.76) that assesses six cognitive domains (memory; visuospatial ability; executive function; attention, concentration or working memory; language; and temporo-spatial orientation). It is out of a total score of 30 points, and a correction of one point can be made in the case of subjects with fewer than 12 years of schooling. The cut-off point for the detection of mild cognitive impairment in its original version is 26. This test has been used to assess cognitive impairment of people with long COVID-19 [78,79].(b)The Symbol Digit Modalities Test (SMDT) will also be used to detect dysfunction related to divided attention, visual tracking, perceptual, and motor speed and memory, both in children and adults, and with a test-retest reliability of between 0.84 and 0.93 in a sample of healthy adults. It consists of converting a series of 120 symbols of different shapes into the numbers that correspond to each one following the key provided. This must be conducted consecutively and as quickly as possible within 90 s after completing a 10-digit practical test. The total score is obtained by counting the number of correct substitutions completed out of a maximum score of 110. A score below 33 is considered a clear indicator of some type of cognitive disorder [80,81].(c)To measure short-term memory impairment, the Spanish version of the Memory Impairment Screen (MIS) will be used. This brief test assesses the existence of memory disorders using free recall (without clues) or selective recall (with semantic clues) of four words. In dementia screening, it presents adequate interobserver (0.85) and test–retest (0.81) reliability. Two points are awarded per word obtained by free recall and one point per word recalled with the help of semantic clues. The total scores range from zero to eight, with a score of four or less indicating possible cognitive impairment [82,83].(d)To assess whether verbal fluency is affected, the Semantic Verbal Fluency Test (Animals) (test-retest reliability of 0.68) will be used, which consists of counting the number of correct words reproduced in 1 min within the category ‘Animals’. Normally, a person without impairment will be able to reproduce about 16 words in 1 min [84,85].-Functional physical variables:(a)Cardiorespiratory capacity will be measured by a 6 min walk test (6MWT) [86]. It is a functional cardiorespiratory test that measures the maximum distance a subject can walk for 6 min. The test measures and records baseline and post-test heart rate, oxygen saturation (SpO2), and dyspnea according to the Borg scale [87]. The 6MWT walk had good test-retest reliability (88 < R < 94). We will use the most recent official Spanish version [88].(b)Leg strength and endurance will be measured by Sit to Stand Test [89]. We will use 30-s Sit to Stand Tests, which are used specifically to test for respiratory diseases [90]. The test evaluates endurance at a high power, speed, or velocity in terms of muscular or strength endurance by recording the number of times a person can stand up and sit down completely in the space of 30 s. The 30-s chair stand has good test-retest reliability (84 < R < 92). We will use the 30 s Sit to Stand Test that has been translated in Spanish and used for COVID-19 patients [91].-Affective state through the Hospital Anxiety and Depression Scale (HADS) questionnaire [92]. The HADS is a scale based on self-report that was developed to detect depression and anxiety disorders in medical patients in primary care settings. The HADS includes 14 items that assess symptoms of anxiety and depression (HADS-A and HADS-D, respectively), with each item corresponding to a 4-point (zero to three) scale, with scores ranging from 0 to 21 for symptoms of both anxiety and depression, with higher scores indicating more severe symptoms. The HADS has been translated into a number of languages, including Spanish [93], to facilitate its use in international trials [94].-Sleep quality through the Insomnia Severity Index (ISI). The ISI [95] works through self-reporting and measures a patient’s perception of nocturnal and diurnal symptoms of insomnia: difficulties initiating sleep, staying asleep, early morning awakening, satisfaction with current sleep pattern, interference with daily functioning, noticeability of impairment attributed to sleep deprivation, and degree of distress or concern caused by sleep deprivation. This scale has seven items, with each answer ranging from zero to four, and an overall score ranging from 0 to 28, with a higher score indicating a higher severity of insomnia. The Spanish version of the ISI [96] shows an adequate internal consistency (Cronbach alpha = 0.82). It has also been used in other studies of people with long COVID-19 [97].

Social support will be measured by the Medical Outcomes Study Social Support Survey (MOS-SS) [98]. It is a self-report instrument consisting of four subscales (emotional/informational, tangible, affectionate, and positive social interaction) and an overall functional social support index. It has good reliability (Cronbach’s alpha ≥ 0.91) and is quite stable over time. It has 19 items, as well as a 5-point Likert Scale. Higher scores indicate more support. We will use the official Spanish version [99]. Community social support will also be assessed using the Perceived Community Support Questionnaire (PCSQ) [100], which provides information on social resources as perceived by the members of the community. It consists of 25 questions assessing four aspects: community integration, community participation, social support from informal systems, and social support from formal systems. It is a Likert-type questionnaire with a scale of one to five. The authors have identified the reliability of the different scales to range between 0.75 and 0.88, which was assessed using the Cronbach’s alpha coefficient [100,101]. In previous research, it has been found to provide an adequate assessment of community experiences of both adults and young people [102]. 

-Physical activity will be measured using the International Physical Activity Questionnaire-Short Form (IPAQ-SF) [103]. It assesses the levels of habitual physical activity over the preceding seven days. It has seven items and records activity at four levels of intensity: vigorous-intensity activity and moderate-intensity activity (walking and sitting). We will use the official Spanish version [104]. IPAQ-SF has sufficient validity for the measurement of total and vigorous physical activity and poor validity for moderate activity and good reliability [105].-Adherence to a Mediterranean diet will be measured using the 14-item Mediterranean Diet Adherence Screener (MEDAS), encouraging compliance to a Mediterranean diet [106]. It includes items on food consumption and intake habits. The total score ranges from 0 to 14, with a higher score indicating greater adherence to the Mediterranean diet [107].-Personal constructs. The personal factors relating to behaviour that will be collected are the following:(a)Self-efficacy will be measured using the Self-Efficacy Scale-12 [108]. The original scale consisted of 17 items that are scored on a 5-point Likert scale. Woodruff and Cashman [109] obtained a factor structure, based on the original 17-item scale, that represented the three aspects underlying the scale, i.e., willingness to initiate behavior, `Initiative’, willingness to expend effort in completing the behavior, `Effort’, and persistence in the face of adversity, `Persistence’. Five items were excluded because of low item-rest correlations and ambiguous wording, resulting in a 12-item version of the scale (GSES-12). This scale has 3 factors: Initiative (willingness to initiate behavior), Effort (willingness to make an effort to complete the behavior), and Persistence (persevering to complete the task in the face of adversity). Internal consistency of the original scale was 0.64 for initiative, 0.63 for effort, and 0.64 for persistence. The total scale obtained a Cronbach’s Alpha coefficient of 0.69 [110].(b)Patient activation in their own health will be measured using the Patient Activation Measure (PAM) questionnaire with regard to the management of their health [111]. It evaluates the patient’s perceived knowledge, skills, and confidence to engage in self-management activities through 13 items with a Likert Scale from one (strongly disagree) to four (strongly agree). The resulting score ranges between 13 and 52. Higher scores indicate higher levels of activation. There is only an official Spanish version for chronically ill patients. It has an item separation index for the parameters of 6.64 and a reliability of 0.98 [112].(c)Health literacy will be measured using the Health Literacy Europe Questionnaire (HLS-EUQ16) [113]. Health literacy is defined as the knowledge of the population, their motivation, and their individual ability to understand and make decisions related to the promotion and maintenance of their health. The questionnaire consists of 16 items, scored between 1 (very easy) and 4 (very difficult). The score of each subject was obtained as the sum of the scores of the 16 items. The final score can be transformed into a dichotomous response: very difficult and difficult = 0, as well as easy and very easy = 1. Higher scores indicate worse health literacy. It presents a high consistency (Cronbach’s alpha of 0.982) in the official Spanish version [114].-For the analysis of the cost-efficiency, the Client Service Receipt Inventory will be used [115], collecting information on the entire range of services and support used by study participants. It retrospectively collects data on the use of services over the preceding six months (e.g., rates of use of individual services, mean intensity of service use, rates of accommodation use over time). We will use the official Spanish version [116].

#### 2.2.8. Statistical Analysis 

Analysis of the outcomes at baseline consist of the following measures. First, descriptive analysis of all of the variables (frequencies for categorical variables; means and standard deviation for continuous variables) will be carried out. A univariate analysis (one-way ANOVA and chi-square) will be used to examine the data and test whether there are baseline differences between groups after randomisation.

Statistical analyses will be chosen based on the sub-sample size (parametric or non-parametric tests). Data collection and statistical analyses will be performed using Excel software, SPSS software (version 25.0) [117], and the R statistical software environment (version 3.6.2) [118]. 

Clinical effectiveness analysis: The report of the results will follow a pre-specified plan based on CONSORT guidelines [119] in order to compare the two groups. Initially, a descriptive comparison (proportions, means, or medians) will be carried out between groups for prognostic variables in order to establish their baseline comparability after randomisation. To analyse the clinical effectiveness, a repeated-measure linear regression will be conducted, including all evaluations over time. For this purpose, the main variable, SF-36 score, will be used as a continuous variable. The models will include adjustments for the baseline value of the SF-36 and for any other variable that would show differences in the baseline measurement. Possible group per time interactions will be examined using linear regression. Similar analyses will be carried out using the secondary outcomes (number and severity of persistent symptoms, Montreal Cognitive Assessment, Sit-to-Stand Test, and HAD test). To counteract the problem of multiple comparisons we will use Bonferroni correction.

Cost-efficiency and cost-utility analysis are as follows. The effectiveness of the interventions will be estimated using the difference between the SF-36 score at the baseline and at the three and six-month follow-up, and the utility will be estimated using QALYs at the three and six-month follow-up. QALYs will be calculated based on these scores using the Spanish EQ-5D tariffs [120]. Along with the number and severity of the ongoing symptoms, scores will also be used as an outcome for the analysis. Cost-efficiency will be explored through the calculation of incremental cost-efficiency ratios (ICERs) for the intervention group using the TAU group as the control. ICER is defined as the ratio between incremental costs and incremental effectiveness. In the same way, cost utility will be explored through the calculation of incremental cost-utility ratios (ICURs), which are defined as the ratio between incremental costs and incremental utilities measured on QALYs. QALYs gained in each evaluation are approximated by using the area under-the-curve technique [121]. Total costs will be calculated by adding direct and indirect costs. Direct costs will be calculated by adding the costs derived from the medication and the use of health services and clinical tests. The medication costs will be calculated by determining the price per milligram during the study period according to the Vademecum during the last year of the study, including value-added tax (VAT). The total cost of drug treatment will be calculated by multiplying the price per milligram by the daily dose in milligrams and the number of days the treatment is received. Costs derived from the use of health services will be calculated considering the data from the Oblikue database [122]. Indirect costs will be calculated based on the number of days taken on sick-leave and multiplying them by the Spanish minimum daily wage during the study period 2019–2020. We assume that data will be missing at random (MAR). Only patients with both cost and relevant outcome data at three and six-month follow-up will be included in the cost-efficiency and cost-utility analyses. Notwithstanding, sensitivity analysis imputing missing three and six-month data will test the robustness of the cost-efficiency and cost-utility results. The imputations will be performed using the package “mice” [123], freely available in cran-R [118].

Variables collected, instruments, and measures are shown in Table 1. 

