#### 2.2.3. Sample Size

To calculate the sample size, we will use the data obtained in the study of Dalbosco-Salas et al. [34] because the intervention is similar to ours, and it is developed in PHC, despite being a clinical trial. To the best of our knowledge, to date there are no studies carried out with post-COVID-19 patients that evaluate a similar intervention with a clinical trial methodology. We will use the difference pre-post score of the short-form 36-item questionnaire (SF-36), the value of the possible highest standard deviation (SD), and a minimum expected difference of 19.3 points in the pre-post rating, which were all taken into account. Accepting a risk alpha of 0.05 and a power of 95% in a bilateral contrast, 70 subjects would be required. A maximum loss-to-follow-up rate of 10% has been estimated. The total sample required is 78 subjects, distributed between the two groups (control–intervention).

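### Holm's step-down procedure would be a cheap improvement on the stated Bonferroni correction, though Bonferroni itself is valid

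*Protocol article*

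**What the plan says.** Section 2.2.8 (Statistical Analysis) sets out a repeated-measures linear regression in which "the main variable, SF-36 score, will be used as a continuous variable". It then extends the approach: "Similar analyses will be carried out using the secondary outcomes". The list reads "secondary outcomes (number and severity of persistent symptoms, Montreal Cognitive Assessment, Sit-to-Stand Test, and HAD test"). The next sentence is "To counteract the problem of multiple comparisons we will use Bonferroni correction". The article does not say which tests form the family.

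Section 2.2.3 (Sample Size) rests on SF-36 only: "Accepting a risk alpha of 0.05 and a power of 95% in a bilateral contrast, 70 subjects would be required". No power target is given for any secondary outcome.

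**The concern.** The method is named outright, so this is not a detail left to an unseen analysis plan. Single-step Bonferroni holds every one of m tests to α/m. Holm holds only the smallest p-value to that threshold and relaxes it for each following one, with the same family-wise guarantee.

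In a trial of about 70 evaluable patients, some real effects on symptoms, cognition, leg strength or mood could be declared under Holm and missed under Bonferroni. This matters most if benefit is broad, as the app's separate modules intend. The study's main conclusion on SF-36 is not at stake.

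**Working it through.** **Inputs from the article.** Two-sided alpha 0.05 and 70 evaluable patients (section 2.2.3). Five listed secondary outcomes (section 2.2.8), or six if the anxiety and depression subscales described in section 2.2.7 are tested separately.

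**Assumptions, not in the article.** 1:1 allocation, so 35 per arm; one group contrast per outcome with a normal test statistic; correlation 0.4 between outcomes; true effects of 0.3, 0.5 or 0.7 SD.

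**The plan's own figure.** With "A maximum loss-to-follow-up rate of 10% has been estimated", 70 / 0.9 = 77.8, rounded up to the stated 78. The 70 cannot be checked directly because the SD is described ("the value of the possible highest standard deviation (SD") but given no value. For 35 per arm the implied SD is 19.3 / [(1.960 + 1.645) × √(2/35)] = about 22.4. This concerns SF-36 alone and is unaffected by the choice between Bonferroni and Holm on secondary outcomes.

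**Why Holm never rejects less.** Order the p-values. Holm compares the j-th smallest with α/(m − j + 1) and stops at the first failure. For m = 6 the thresholds are 0.05/6 = 0.0083, 0.05/5 = 0.0100, 0.05/4 = 0.0125, 0.05/3 = 0.0167, 0.05/2 = 0.0250 and 0.0500. Bonferroni uses 0.0083 throughout. Any p-value at or below 0.0083 therefore also passes Holm.

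**Why the error control is the same.** With m0 true nulls, the first true null to be rejected must fall at step m − m0 + 1 or earlier, so its threshold is at most α/m0. The chance that any of the m0 null p-values falls that low is at most m0 × α/m0 = α. Like Bonferroni, this needs no assumption about dependence.

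**Bonferroni power by formula (six tests).** The critical value is 2.638. The expected test statistic is d × √(35/2) = 4.183d.
- d = 0.7: Φ(2.928 − 2.638) = Φ(0.290) = 61.4%.
- d = 0.5: Φ(2.092 − 2.638) = Φ(−0.547) = 29.2%.

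**Simulation (six tests, correlation 0.4, 100,000 runs).** Average power per truly affected outcome, Bonferroni against Holm:
- 0.7 SD, one affected: 61.7% against 61.7%.
- 0.7 SD, two affected: 61.4% against 62.7%.
- 0.7 SD, three affected: 61.3% against 64.3%.
- 0.7 SD, four affected: 61.5% against 66.4%.
- 0.7 SD, all six affected: 61.6% against 72.5%.
- 0.5 SD, two affected: 29.2% against 30.0%.
- 0.5 SD, four affected: 29.2% against 32.0%.
- 0.5 SD, all six affected: 29.0% against 35.3%.
- 0.3 SD, all six affected: 8.4% against 9.7%.

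Small differences in the Bonferroni column are simulation noise around the formula values. With five tests, all affected at 0.7 SD, the figures are 63.9% against 74.2%.

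**Other measures, same settings.**
- Chance of at least one true finding: equal to within 0.1 point in every scenario.
- Chance of showing all six when all respond at 0.7 SD: 19.6% against 46.5%.
- Chance of any false positive when four of six respond at 0.7 SD: 1.6% against 3.2%.

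**Familywise error.** Separate runs with no true effect, using five or six tests and correlation 0 or 0.5, gave 0.041 to 0.049, identical for the two methods.

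**The case against.** The strongest reply is that this is a preference between two sound methods. Bonferroni is standard, pre-specified and conservative. It holds the family-wise error, conflicts with no other statement, and breaks no power claim, because none is made for secondary outcomes. All of that stands.

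Three further points also stand:
- The family is not defined. The sentence could cover time points, SF-36 scales or interactions as well as secondary outcomes, so the size of any loss cannot be derived from the article. Defining the family may also be left to a fuller plan, so its absence here is not held against the article.
- The largest gains need a true effect of 0.5 to 0.7 SD on every outcome at once. Nothing in the article establishes that.
- A reader might infer that Bonferroni gives power away for nothing. It does not. Its realised error on true nulls is lower when some outcomes respond (1.6% against 3.2% above), and its simultaneous intervals are simple and agree with its tests.

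None of this alters the ordering of the two methods for testing: at the same nominal family-wise level, Holm can tie with Bonferroni or reject more, never less.

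**Conclusion.** The point holds as a low-cost improvement. With six tests, correlation 0.4 and 35 per arm, moving to Holm adds about 0 points of average power per truly affected outcome with one true effect, 1 to 5 points with two to four true effects of 0.7 SD, and 6 to 11 points when all six respond at 0.5 to 0.7 SD. At 0.3 SD the gain is only about 1 point even if all six respond. Power to find at least one effect is practically unchanged.

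The number of tests, the correlation, equal allocation and the effect sizes are assumptions; only alpha and the 70 evaluable patients come from the article. The point also relies on reading the correction as applying to the listed secondary outcomes, which the order of the sentences suggests but does not state.

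A reader might go further and infer that Bonferroni is an error, or that it undermines the 95% power for SF-36. The article supports neither: the method does what it is said to do, and nothing states that the primary SF-36 contrast is part of the corrected family.

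**What to change.** In section 2.2.8, replace Bonferroni correction with Holm-Bonferroni correction and add that it applies to the listed secondary outcomes. That is one word and one clause. No new data or change of sample size is needed, and R, already named in that section, can do the adjustment.

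Two costs should be accepted knowingly. Simultaneous confidence intervals are less direct under Holm; unadjusted intervals can be shown beside Holm-adjusted p-values, labelled as such because the two may disagree. Realised error on true nulls rises slightly but stays at or below 5%. If matching simultaneous intervals matter more to the investigators than the extra power, keeping Bonferroni is defensible.
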